### Setting

2.4

We are conducting the study at LMU University Hospital, a center renowned for its high‐end medicine, nursing, medical innovation, and research. With over 2,000 beds, LMU Hospital is a highly advanced hospital that encompasses all fields of medicine.

For this study, we selected four intensive care units, one intermediate care unit, and three general wards. These wards were chosen due to their notably high incidence of patients with pressure injuries (PI) or incontinence‐associated dermatitis (IAD), reflecting the specific diseases treated and the demographics of their patient populations. These wards differ in terms of medical specialty and the number of staff, ranging from 33 to 54 employees (average 45.8) in the intensive care and intermediate care units, and from 15 to 28 employees (average 23) in the general wards. The nursing and ward managers agreed to participate in this study. In addition, consent was obtained from the Staff Council, the Data Protection Officer, and the Ethics Committee of the LMU Medical Faculty. Additionally, before the commencement of the study, we confirmed that the selected wards had adequate Wi‐Fi coverage to support the use of the AI‐based application on tablets and smartphones.

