### Sample Size

2.6

Based on current methodologies, we performed an a priori sample size calculation using power analysis (Döring and Bortz 2016) with the G*Power 3 software (Faul et al. 2007). For this calculation, we assumed moderate effect sizes between dependent and independent variables (Cohen 1988), an alpha level of 0.05, and a power of 0.80. To test correlations between dependent variables (task load, time, guideline adherence) and four independent variables (use of the demonstrator, general load of the shift, professional experience, severity of wound) using multivariate models (multiple linear regression) under these assumptions, we will require a total of 85 nurses.

With a calculated sample size of 85 nurses and considering up to four independent variables, we anticipate obtaining meaningful results within a manageable timeframe and with the available resources. Accounting for a projected 10% dropout and missing rate, based on experiences from previous studies, we plan to recruit 95 nurses to ensure a sufficiently large sample for subsequent evaluation.

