Potential challenges in implementing the AI‐based application in a clinical setting include technical issues, such as ensuring full Wi‐Fi coverage, and meeting hygiene requirements, such as disinfecting tablets. Another common hurdle in technology intervention studies is user acceptance. However, in the realm of technologies that support nursing tasks, studies have shown high technology acceptance (Zöllick et al. 2020). We therefore anticipate high acceptance due to the simplification of wound care and documentation processes. To further enhance user acceptance, local wound experts and ward managers have been involved in the development of the application and will be key users during its implementation on the wards. Additionally, the implementation will be supported by comprehensive training measures to ensure safe use and handling of the application and AI predictions. This is crucial, especially when addressing incorrect or inaccurate predictions made by AI and the ethical challenges that arise in biomedical AI (Mittelstadt et al. 2016).

As this study is monocentric, focusing only on nurses at one university hospital, the external validity is limited. Another limitation is the constrained resources of the project, which preclude the use of a randomized study design and may introduce slight biases due to the consecutive and non‐randomized observation of control and intervention groups, as well as the absence of blinding. Moreover, the organization of information events and recruitment of nursing staff may heighten awareness of pressure injury and IAD care, potentially influencing care and documentation and thus the results of the study. Organizational delays, which are inevitable due to clinical processes, may also introduce bias. We also acknowledge that factors such as ward affiliation might influence outcomes, but were not included in this exploratory pilot study due to the complexity of the models required and the limited sample sizes. For this reason, only the most crucial factors, from an expert perspective, were included in the analysis.

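### Ward type is left out of an unrandomised before-after comparison for reasons that do not rule out a single care-level term

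*Protocol article*

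**What the plan says.** All references are to the protocol article.

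- **Design (2.3, 2.11).** A control phase (May 2023 to January 2024) is followed by an intervention phase that began in July 2024. There is no randomisation.
- **Wards (2.4).** The sites are mixed: "we selected four intensive care units, one intermediate care unit, and three general wards". The section says they differ in specialty and staffing.
- **Recruitment (2.7).** Wounds enter as they are reported, and only if the nurse in charge agrees. Nothing sets how many observations come from each ward or ward type in each phase.
- **Models (2.6, 2.12).** Each outcome gets its own linear regression. The sizing names "four independent variables (use of the demonstrator, general load of the shift, professional experience, severity of wound". One of these is the exposure, so there are three covariates, and none describes the ward. The demonstrator's contribution is judged by its t-test and by comparing the models with and without it.
- **Reason for omitting ward (3, Discussion).** The article concedes that "factors such as ward affiliation might influence outcomes, but were not included in this exploratory pilot study due to the complexity of the models" and adds limited sample size as a second reason. It says that the factors kept were those experts judged most important.

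**The concern.** In a before-after comparison without randomisation, any change in the kind of ward supplying the observations moves together with the intervention. Intensive and general care could plausibly differ in how long wound care takes, how loaded nurses feel and how care is carried out. All the models are therefore exposed.

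The three covariates do not clearly stand in for care level. Severity describes the wound, experience describes the nurse, and shift load is rated relative to the average (2.10), so it may miss an absolute difference between an ICU and a general ward.

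The stated reason concerns ward affiliation, a factor with eight levels. The article does not consider the coarser split into ICU/IMC and general ward, which is one 0/1 term. Section 2.12 already dummy-codes severity and the 5-point shift-load rating, and the latter alone can use four degrees of freedom. One more is hard to refuse as too complex.

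**Working it through.** **1. The plan's own figure.** From 2.6: "an alpha level of 0.05, and a power of 0.80", four predictors, and "we assumed moderate effect sizes between dependent and independent variables". No number is given for the effect size. Taking Cohen's f² = 0.15 (assumption), the omnibus F test has u = 4 and N − 5 degrees of freedom, with noncentrality λ = f² × N.

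- N = 85: λ = 0.15 × 85 = 12.75, df 4 and 80, power 0.803. This reproduces "we will require a total of 85 nurses" and supports the value taken for f².
- With "a projected 10% dropout and missing rate": 85 / 0.90 = 94.4, rounded up to 95, as stated.

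**2. What an unequal ward mix would do.** Assumptions, none from the article: no AI effect, 42.5 observations per phase, a gap of d between ICU/IMC and general wards in units of the within-type SD, and no part of that gap absorbed by the three covariates.

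- Bias = (share in phase 1 − share in phase 2) × d.
- Variance per phase = 1 + d² × p × (1 − p).
- SE = √(mean variance × 2 / 42.5).
- False-positive rate from the noncentral t, 80 df, two-sided 0.05.

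Worked case, 70% versus 50%, d = 1: bias = 0.20 × 1 = 0.20 SD. The variances are 1.21 and 1.25, mean 1.23. SE = √(1.23 × 2 / 42.5) = 0.241, so the noncentrality is 0.20 / 0.241 = 0.83 and the rate is 13.0%.

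| ICU/IMC share by phase | d | Bias (SD) | False positives |
|---|---|---|---|
| 60% / 60% | 0.5 to 1 | 0 | 5.0% |
| 70% / 50% | 0.5 | 0.10 | 7.3% |
| 70% / 50% | 1 | 0.20 | 13.0% |
| 80% / 40% | 0.5 | 0.20 | 14.4% |
| 80% / 40% | 1 | 0.40 | 38.3% |

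A simulation of 4,000 runs at 70% versus 50% agrees: 7.3% (d = 0.5) and 12.8% (d = 1) without the care-level term, and 5.5% in both cases with it.

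**3. Cost for the demonstrator term.** Single-coefficient test, u = 1, f² = 0.15, N = 85.

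- Power is 0.9415 with four predictors and 0.9414 with five. Required N is 55 either way.
- If care level is correlated with phase, precision drops. At 70% versus 50%, the squared correlation is 0.20² × 0.25 / (0.6 × 0.4) = 0.042, the variance inflation is 1 / (1 − 0.042) = 1.04, and power is 0.93. At 80% versus 40%, the inflation is 1.20 and power is 0.90.
- The level of 0.94 depends on f² = 0.15 for this one term. With a 0.5 SD effect (f² = 0.5² / 4 = 0.0625), power is 0.62 with either four or five predictors. The added cost is negligible in both cases.

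**4. Cost on the plan's own basis.** Omnibus test with five predictors: required N is 92, and power at 85 is 0.764 instead of 0.803. The plan's "we plan to recruit 95 nurses" would leave 95 × 0.90 = 85.5 after planned losses. Reaching 92 from 95 allows losses of only 3 / 95 = 3.2%.

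**The case against.** The strongest reply is that the omission is disclosed and reasoned. The article names ward as a possible influence, says why it was left out and by what rule covariates were chosen, and calls the study exploratory. Choosing covariates in a small pilot is partly judgement. For full ward affiliation the reason has force: seven dummies make 11 predictors, which needs N = 123 on the omnibus basis and gives power of 0.58 at 85. It does not carry over to one binary term, and disclosing a possible confounder does not adjust for it.

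Other parts of the reply stand:

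- The shares and gaps in the illustration are assumed. The same wards are planned for both phases, and 2.8 expects no change in infrastructure or processes. The existing covariates may absorb part of any ward-type difference.
- A reader might infer that one binary term would remove ward confounding. It would not. It handles an additive ICU/IMC-versus-general difference. Shifts among wards of the same type, and changes over calendar time, remain.
- A reader might also infer that the term is free. That is practically true for the demonstrator coefficient, but not for the omnibus sizing in 2.6.
- The article does not say that ward was recorded for each control observation. That phase is closed and its data are anonymised. Giving modelling reasons for the omission does not show that the variable exists.

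**Conclusion.** The point holds as an avoidable risk. The stated reasons do not justify leaving care level out of the models. Without it, the AI estimate is open to bias equal to the change in ICU/IMC share times the ward-type gap: 0.10 to 0.20 SD, with 7% to 13% false positives, at 70% versus 50% and a gap of 0.5 to 1 SD. These figures rest on assumed shares and gaps, equal phases and no absorption by the other covariates.

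The documents do not support the stronger reading that the comparison is in fact confounded by ward. They do not report the mix by phase, and with equal shares the bias is zero. The omission is also not hidden, and it contradicts nothing else in the article.

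**What to change.** In 2.12, provided ward or care level was recorded or can be recovered for the control phase, add care level (ICU/IMC versus general ward) to every model as the fourth covariate and fifth predictor. State that shifts between wards of the same type and calendar-time changes stay unadjusted. If care level cannot be recovered, say so and keep the limitation.

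The cost is one degree of freedom per model and a change to 2.6, which has two options:

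- Keep the omnibus basis and restate it: either N = 92 (92 / 0.90 = 102.2, so 103 recruited at the planned loss) or power of 0.76 at 85. Control recruitment has closed, so extra nurses could come only from the intervention phase.
- Base the sizing on the demonstrator term, which is the contrast to be interpreted. Power at 85 is then about 0.94 at f² = 0.15, or about 0.93 if the shares are 70% and 50%. The effect size assumed for that term should be given as a number.

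A model with ward fixed effects (7 df) is an optional sensitivity analysis, not a required change. A count of observations by ward type and phase in the results would show whether the risk materialised; its absence from this article is not a fault.

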## Data Availability

The data that support the findings of this study are available from the corresponding author upon reasonable request.
